### Monitoring

The co-principal investigators (MPIs: GC and HT) at UCSF and the University of Pennsylvania will be responsible for study oversight, including data quality assurance and regulatory compliance for adverse event reporting. The study team, including the project manager, co-investigators, data managers, local study coordinators, and research assistants, led by the MPIs, will monitor the progress of the study including recruitment, retention, adverse events, and other challenges on weekly study calls.

To ensure the safety of participants and the integrity of the data, study data will be reviewed every 6 months by an independent data safety monitoring board (DSMB). DSMB members are independent of the study and have no financial, scientific, or other conflict of interests with the trial. The DMSB will review all adverse (AE) and serious adverse events (SAE), as well as enrollment and retention data. The responsibilities of the DSMB will include identifying any patterns of adverse events in accumulated AE reports and reviewing fidelity to the intervention. Following each report, the DSMB will make recommendations on the continuation of the study, as well as provide feedback on any specific challenges or questions posed by the study team.

Safety monitoring will be the responsibility of the MPIs, who will review all AE and SAE reports shared by the field team. Adverse events and harms will be identified through participant report at the single follow-up visit, if and when participants return for HIV retesting. Safety reporting formats and timelines for AEs, SAEs, and other incidents or harms will follow guidelines set forth by the UCSF Institutional Review Board (IRB), the local IRBs and Research and Ethics Committees (RECs) in Kenya and Uganda, and the National Institute of Health (NIH), respectively. All AEs will be documented in study logs, along with their relevant reporting status.

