#### Participant timeline and procedures

Immediately following enrollment, participants will complete a brief baseline survey including questions on demographics and recent HIV risk factors. Following the baseline survey, they will be randomized to one of the 12 study arms and, if assigned to one of the 10 messaging intervention arms, they will be shown the associated baseline video message. The study software will be programmed to automatically show only the video message for the study arm to which the participant has been randomized, to reduce possible human error. All participants will be reminded to return for another HIV test 3 to 6 months after the baseline visit. Participants who return for a repeat HIV test at follow-up will receive standard HTS through the hospital or clinic and will complete a brief follow-up study survey to assess HIV risk factors since baseline enrollment. The study team will record HIV test results as well. Participants who have been assigned to the incentive arm and return for retesting at follow-up will receive a small financial incentive (up to $5 USD) at the time of retesting. The schedule of study enrollment, interventions, and assessments is detailed in Table 2. Participants may seek and receive any concomitant care during their participation in this trial.

**Table 2 Tab2:** SPIRIT figure: schedule of enrollment, allocation, interventions, and assessments in the IBIS megastudy

	Enrollment	Post-allocation		Close-out	Post-close out
Timepoint	Baseline	*t* + 8 weeks	*t* + 11 weeks	*t* + 12 weeks–*t* + 24 weeks	*t* + 25 weeks–*t* + 48 weeks
Enrollment:					
HIV testing*	X			X	
Eligibility screen	X				
Verbal consent	X				
Allocation	X				
Interventions:					
[Control arm]	X				
[Incentive arm]	X			X	
[Messaging arms, *n* = 10]	X	X	X		
Assessments:					
Questionnaire	X			X	
Post-follow up survey for non retesters**					X

^*^ HIV testing is conducted per Ministry of Health (MoH) standard of care and is not a study procedure; HIV test results will be documented on study case report forms (CRFs)

^**^ We will reach out to a small sample of participants who did not return for HIV retesting to see if they tested elsewhere and, if not, to ask about their reasons for not retesting

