#### Outcomes

The primary outcome will be HIV retesting at any study venue 3–6 months after the initial baseline HIV test. We will use either participant demographic information (such as name, phone number, birthdate) and/or national identification number or electronic medical record number (if available) at baseline and time of retesting to verify participant identity (using procedures we have used in prior studies [5, 40]) and measure HIV retesting.

The secondary outcome will be PrEP referral acceptance (i.e., willingness to be referred to the PrEP clinic) among participants who retest HIV-negative and are not taking PrEP at time of retesting. We will measure acceptance of referral to PrEP services at time of retesting. Other outcomes will include the proportion of persons who test HIV positive (i.e., seroconvert) among participants who retest for HIV, as well as linkage to care and ART-initiation among those who seroconvert.

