### Sample size

We made the following assumptions in determining the sample size and minimum detectable effect sizes. With 64,000 adults (≥ 15 years) testing for HIV in 2023 at the eight study HIV testing service sites and a reported HIV positivity of ~ 2%, we estimate there are about 62,700 HIV-negative adults tested per year in these study communities. We estimate that about 50% of adults (about 31,000/year) accessing HIV testing at HIV clinic sites will be classified as being at increased risk of HIV infection based on their self-reported answers to risk screening questions and thus will require quarterly HIV retesting. Based on our prior HIV retesting studies in Uganda, we anticipate at least 90% of eligible adults will agree to participate in the megatrial [29, 32]. With enrollment over 18–24 months, we anticipate enrolling 30,000–40,000 participants in the trial, with a range of 2500–3333 participants per arm in a 12-arm trial.

Based on our previous retesting study in Uganda, we assumed that 38% of the control group will retest for HIV within 6 months [29]). With a sample size of at least 3000 participants/arm, we will have 80% power to detect a 4.7 percentage-point difference in HIV testing for any of the intervention groups compared to the control group. These power calculations account for multiple hypothesis testing by using a Bonferroni correction and setting the significance level to 0.00455 (i.e., 0.05/11 comparisons between interventions and control). This is a very conservative approach; however, since we will have more statistical power in our analyses by using the Benjamini and Hochberg Procedure to control the false discovery rate [41] and covariate adjustment will also improve efficiency. Thus, in practice we expect to be able to detect differences between each intervention group and the control group that are smaller than 4.7%.

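### Harms are identified only at the retest visit, which is itself the primary outcome, so a projected 58–62% of participants have no described harm assessment

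*Protocol article*

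**What the plan says.** The Monitoring section of the protocol article gives one route by which harms come to light: "Adverse events and harms will be identified through participant report at the single follow-up visit, if and when participants return for HIV retesting". The visit in question is also the endpoint. The Outcomes section says: "The primary outcome will be HIV retesting at any study venue 3–6 months after the initial baseline HIV test". A participant who does not retest has no such visit.

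The one contact planned with people who did not retest is a post-close-out survey at weeks 25 to 48, described in a footnote to Table 2 (Participant timeline and procedures): "We will reach out to a small sample of participants who did not return for HIV retesting to see if they tested elsewhere". Those who did not are to be asked why. The footnote does not mention harms.

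Under Monitoring, an independent DSMB meets every six months. It sees adverse and serious adverse events together with enrolment and retention figures, and is asked to look for patterns in the accumulated reports. The article does not say whether events are compared between arms, or over which denominator.

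**The concern.** Whether a participant is asked about harm depends on the behaviour the trial is trying to change. Two consequences follow.

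First, most participants are never asked, and the loss may be informative. The ten messaging arms send SMS reminders at 8 and 11 weeks. Eligibility requires that a phone be available every day, not that it be private. Table 1 itself lists stigma among the barriers to retesting. A participant whose HIV-related message was seen by someone else could be harmed and could stay away for that reason. Control and incentive participants receive no SMS, so any such loss could differ by arm.

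Second, an arm that brings more people back asks more people about harm. Its raw event count rises with retesting even if its true harm rate equals that of control.

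At stake is the safety statement the trial can make about low-cost messages meant for wide use. No efficacy estimate is affected.

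**Working it through.** **Inputs from the Sample size section.** Control rate: "we assumed that 38% of the control group will retest for HIV within 6 months". Detectable effect: "we will have 80% power to detect a 4.7 percentage-point difference in HIV testing for any of the intervention groups compared to the control group", hence 38% against 42.7%. Arm size for power: "With a sample size of at least 3000 participants/arm". Enrolment: "we anticipate enrolling 30,000–40,000 participants in the trial, with a range of 2500–3333 participants per arm in a 12-arm trial", which implies 12 equal arms. Alpha is 0.05/11 = 0.00455. The article gives no harm rate, so I assume 1%, 2% and 5%.

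**1. The plan's own figure.** For two proportions, two-sided with pooled variance, n = [z(1−α/2)·√(2p̄q̄) + z(0.80)·√(p₁q₁ + p₂q₂)]² / Δ². With p₁ = 0.38, p₂ = 0.427, p̄ = 0.4035, z = 2.837 and 0.842, this gives n = 2948 per arm. Power at 3000 is 0.809 and the detectable difference is 4.66 points. The stated 4.7 points is reproduced. Sidedness is not stated; a one-sided test would need 2593 and does not fit.

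**2. Share with no harm assessment.** U = 1 − (p_control + 11·p_intervention)/12.

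| Retesting in all 11 intervention arms | U | People, of 30,000 to 40,000 |
|---|---|---|
| 38% (no effect) | 1 − 0.380 = 62.0% | 18,600 to 24,800 |
| 42.7% (design effect) | 1 − 5.077/12 = 57.7% | about 17,300 to 23,100 |
| 48% (+10 points, assumed) | 1 − 5.66/12 = 52.8% | 15,850 to about 21,100 |
| 58% (+20 points, assumed) | 1 − 6.76/12 = 43.7% | 13,100 to about 17,500 |

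**3. Raw counts by arm, if compared.** Expected reports = n × retest rate × harm rate among retesters. With equal true harm the ratio to control is p_intervention/0.38: 0.427/0.38 = 1.12, 0.48/0.38 = 1.26 and 0.58/0.38 = 1.53. At the design effect with 3000 per arm:

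- 1% harm: 11.4 against 12.8 reports
- 2% harm: 22.8 against 25.6 reports
- 5% harm: 57.0 against 64.1 reports

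The chance of a nominally significant excess (two-sided 0.05) in the intervention arm is then about 5%, 6% and 9%, against 2.5% with no artefact. A true doubling of harm would show as 2 × 1.12 = 2.25. Per retester, the ratio under equal harm is 1.00, provided return does not depend on harm.

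**4. Selection among returners.** Hold overall retesting at 38% and let harmed people return with probability q (assumed). The rate seen per retester is h × q/0.38. With h = 2%:

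- q = 0.38 gives 2.0%
- q = 0.19 gives 1.0%
- q = 0.10 gives 0.5%
- q = 0 gives 0%

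Changing the denominator does not recover these missing harms.

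**5. What a survey of non-retesters could show.** The article says only that the sample is small. Assume 20 to 100 per arm. Expected events per arm are 0.2 to 1 at 1% harm, 0.4 to 2 at 2%, and 1 to 5 at 5%. If no event is seen, the upper 95% limit is roughly 3/n, that is 3/20 = 15% to 3/100 = 3%. Contact falls 25 − 11 = 14 to 48 − 11 = 37 weeks after the last SMS.

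**The case against.** A reader might infer that the DSMB's comparison of arms would track retesting instead of harm, that an effective arm would look less safe, and that the board could not do its job. The article does not support this. It describes no by-arm comparison and no count per randomised participant. The board also receives retention data, from which events per returner can be formed, and that removes the artefact in step 3. Even raw counts reflect both rates, and at the design effect the inflation is 12%. Larger ratios need retest rates that the article does not plan for.

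It can also be said that the interventions are rated minimal risk under Ethics and consent, that ethics bodies in three countries approved the procedures, and that message content was reviewed in workshops and then piloted. Nothing in the article shows that harmed people return less often. The Table 2 footnote is a one-line summary that does not exclude harm questions, and the full protocol may say more.

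Most of this stands, and it limits both the likely consequence and the strength of the claim. It does not remove the core. The Monitoring sentence is a stated rule and not a detail left out. The minimal-risk rating cannot be checked in non-returners under that rule. The pilot gives little reassurance, since it used the same procedures, enrolled 98 people, and held follow-up visits only in Kenya.

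**Conclusion.** The point holds as a gap in harm ascertainment. Harms are identified only at the visit that constitutes the primary outcome, and the described contact with non-retesters does not fill the gap. The 58–62% without assessment is a projection from the 38% planning rate and the 4.7-point effect; it would be smaller if the interventions worked better than planned.

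The main problem is selection among returners. Its size cannot be known from the documents, and the 19%, 10% and 0% return rates in step 4 are illustrations. Confounding of raw counts with retesting is secondary: it is modest at the design effect, arises only if such counts are compared, and can be corrected with the right denominator. The finding is worth acting on because the remedy is cheap, but it does not threaten the trial's efficacy conclusions.

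**What to change.** - Add the adverse-event questions used at the follow-up visit, covering social harms such as unwanted disclosure, to the survey of non-retesters already planned in Table 2.
- Draw that sample at random within arm, and state its size.
- Log any harm that a participant reports spontaneously at any contact, and amend the Monitoring sentence so that it no longer gives the retest visit as the only route.
- Give the DSMB events by arm with both the number randomised and the number assessed, separately for returners and sampled non-returners.

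The cost is a few more questions in an existing survey and a change to the DSMB tables, with no new visit. Enrolment began in December 2025 and follow-up is expected to end in December 2027, so most contacts can still be covered. The limit should be stated openly: a small sample contacted late can reveal only large or common harms among non-returners, and it cannot support precise comparisons between arms.

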### Dissemination plan

The study’s findings will be prepared for presentation to the scientific community at international and regional academic conferences and for publication in peer-reviewed journals. In addition, findings will be shared with study participants in year 5, through communications in local community dissemination meetings in the study sites. Local community dissemination meetings will be advertised through local leadership structures. We will also prepare documents summarizing the findings and their policy implications for representatives of the Governments of Uganda and Kenya including Ministry of Health officials.

## Discussion

In this trial, we will use an innovative, large, multi-arm (“megastudy”) trial design to compare multiple low-cost behavioral interventions, designed in collaboration with local health care worker and community member input, to promote HIV retesting among persons at high risk for HIV following a baseline negative test in Kenya and Uganda. Ensuring that persons at high risk test regularly for HIV addresses an issue of major public health significance, as frequent, regular HIV testing is a key first step in accessing highly efficacious tools to prevent HIV, ensuring early diagnosis after infection, and achieving prompt ART initiation among people with HIV. As countries approach or meet “95–95–95” targets for HIV treatment and viral suppression, optimizing HIV status awareness and reducing time from HIV infection to diagnosis and treatment initiation is crucial for further reducing HIV incidence. By identifying and implementing low-cost, scalable interventions to promote HIV retesting for individuals at elevated risk of infection across high-volume HTS sites in East Africa, we aim to test and compare multiple interventions in a single trial and thus accelerate discovery of effective (and ineffective) interventions for this public health challenge.

This study has several strengths. By using a megastudy design, we will test multiple behavioral interventions at the same time, across the same populations, and for the same outcome, yielding a like-to-like comparison of efficacy to a standard of care control arm. We will also be able to assess comparative advantages between the interventions. The large sample size will allow for the ability to detect small effects of very low-cost, scalable interventions and to conduct analyses of which interventions work best for key populations. Another study strength is our multi-step adaptation approach to ensure that the intervention content and implementation are acceptable to the local contexts in western Kenya and southwestern Uganda. Our use of avatar videos for intervention delivery has the benefit of controlling intervention consistency across a massive study population rather than relying on counselor delivery, which would have natural variability and possible contamination of messaging across study arms by the counselors. Using avatar videos also allows for low-cost, rapid adjustments based on the workshop and pilot testing feedback; intervention scripts and messengers can be easily and quickly revised, rather than filming new promotional videos with actors.

This study also has several limitations and potential risks. Due to the large scale of the megastudy design, our intervention options were limited to those that could be easily delivered, with low cost and low time burden. We had to eliminate several promising interventions that would have required higher staff numbers and time than was feasible for this trial, such as community-based outreach. There were also some intervention ideas that proposed varying the method of message delivery, such as adding additional follow-up phone calls or including an interactive gamification component. However, varying both the content and method of the interventions in different study arms would have introduced intervention heterogeneity (apart from message content), and thus prevented a clear comparison of messaging content across trial arms. We therefore decided to focus on varying the intervention content while using a standardized delivery method across all study intervention arms (a baseline avatar video and two follow-up SMS messages). Finally, real-world testing in clinical settings is subject to secular trends in testing service delivery that can be impacted by international or domestic funding changes, political turmoil (e.g., elections), or other large-scale events (such as the COVID-19 pandemic). If HIV testing at the participating study clinics is unexpectedly low, it may be challenging to enroll our target sample size of 30,000–40,000 participants. If this situation occurs, we will consider either expanding to additional clinics or using an adaptive design to allow for dropping the least promising interventions at an interim timepoint.

We expect that the methods and results of the IBIS megastudy will provide valuable insights not only for those engaged in HIV service delivery, but also for behavioral scientists who study health-related decision-making and to practitioners working in other areas of public health. Our large sample size will allow for the ability to detect small effects of very low-cost interventions, with the potential for population-level effects when implemented at scale. It will also give us the ability to identify specific interventions that work best for key populations at risk, such as interventions best suited for men and young women, who may respond differently to the intervention message content. We expect to publish results from all 11 intervention arms, including those with null results, thereby reducing publication bias in the field. While other megastudies have been implemented in high-income settings, to our knowledge the IBIS megastudy will be the first of its kind in a low- and middle-income country setting. The methodology can be generalized to many other health problems in low- and middle-income countries (e.g., boosting demand for vaccination). As such, this megastudy has the potential to influence how researchers and programs design and test low-cost, scalable interventions to promote health behaviors. 

## Trial status

The current protocol is version 3.1, as of December 2, 2025. The IBIS megastudy trial is registered under protocol number NCT06971367 in clinicaltrials.gov.

Participatory prototyping workshops were conducted with 53 participants in Kenya in December 2024 and with 52 participants in Uganda in February 2025. The pilot trial is registered under protocol number NCT06785103 in ClinicalTrials.gov. Enrollment of pilot participants occurred from March to April 2025 in Kenya and from May to June 2025 in Uganda. A total of 49 pilot participants were enrolled in each country (98 enrolled overall). Pilot follow-up visits were conducted in Kenya from June to July, 2025. Pilot follow-up visits were unable to be conducted in Uganda due to a temporary delay in funding from the National Institutes of Health (NIH) based on issued Notice Number: NOT-OD-25–104, which introduced a significant policy change regarding foreign (non-US) subawards. Recruitment and enrollment of the IBIS megastudy began on December 9, 2025 and is expected to conclude in June, 2027. Completion of megastudy follow-up visits is expected in December 2027.

## Data Availability

The de-identified final trial dataset, protocol, and statistical analysis plan will be made available without restriction through a publicly accessible data repository.
